Published studies comparing TACE with bland embolization (BE) have demonstrated heterogeneous and contradictory results, with some studies showing superior survival and/or safety outcomes for one technique [5, 6, 9] and others demonstrating equivalent outcomes [8, 19, 20]. One of the potential contributors to these varying results was ambiguity in the World Health Organization (WHO) 2000/2004 NET pathologic grading systems, which were used in many older studies [4, 6, 7, 9, 12, 21] and have since been replaced by the more objective, reproducible WHO 2010 system. In addition to uncertainty about survival outcomes among embolotherapy techniques, the comparative safety profiles and treatment toxicities also remain controversial. Two retrospective series have suggested higher risks for biliary complications after DEB-TACE [13, 22], but there remains no definitive comparison with lipiodol TACE or BE. The combination of an indeterminate evidence base and lack of specific guideline recommendations have contributed to wide variations in clinical practice, manifesting in equivalent use of available embolotherapy techniques for NET liver metastases in a survey of U.S. interventional radiologists [23].

Given the increasing incidence of NET and ongoing questions regarding an optimal treatment algorithm for NET liver metastases, there is a need for a prospective randomized controlled trial (RCT) to elucidate the optimal embolotherapy technique between transarterial BE and chemoembolization. This article presents the study protocol of a prospective, open-label, multicenter RCT using a parallel group assignment and noninferiority design. The trial aims to determine the optimal embolotherapy modality for NET liver metastases by comparing hepatic progression-free survival (HPFS), treatment toxicities, symptom control, and quality of life.

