### Study population

Eligible participants will have liver-dominant NET that is symptomatic, progressive, or with a liver tumor burden > 25% of the liver volume without need for documented progression. Patients with extrahepatic disease progression can be enrolled in the study if they have liver-dominant disease based on the assessment of a multidisciplinary NET care team. Concurrent treatment with somatostatin analogues is allowed. No concomitant radiation therapy, chemotherapy (e.g., capecitabine/temozolomide), biologic therapy (e.g., everolimus, sunitinib), or ablation is allowed. Patients also cannot receive these treatments until after the primary endpoint of hepatic progression is reached. All participants will be consented with an institutional review board (IRB)-approved, site-specific informed consent form prior to undergoing any study-related procedures. Detailed inclusion and exclusion criteria are shown in Table 1. A SPIRIT figure is shown in Fig. 2, and a SPIRIT checklist is available in Additional file 1. Patients may be withdrawn from the study for failure to adhere to protocol requirements or withdrawal of consent.

**Table 1 Tab1:** RETNET trial inclusion and exclusion criteria

Inclusion criteria	Exclusion criteria

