• Participants aged 18 years and older • Biopsy-proven neuroendocrine tumor with tumor burden dominant in the liver • Measurable metastasis to liver with at least one dimension ≥1.0 cm. Known extrahepatic disease should be limited to lymph nodes of < 2 cm and/or any bone metastases. • Liver tumor burden ≤ 70% of the total liver volume by visual estimate • Not a candidate for surgical resection owing to unresectability, anatomy, anesthesia risk, patient preference • Symptoms uncontrolled by somatostatin analogues OR morphologically progressive tumor by RECIST 1.1 criteria in the liver OR baseline tumor burden > 25% of the liver volume • No plans for the patient to receive other concomitant therapy while on this protocol treatment (other than octreotide or bisphosphonate therapy) • Performance status 0–2 on Zubrod performance scale • Serum creatinine ≤ 2.0 mg/dl • Serum bilirubin ≤2.0 mg/dl • Serum albumin ≥3.0 g/dl • Platelet count ≥ 50,000/μl (corrected if needed) • INR ≤ 1.5 (corrected if needed) • All patients must be informed of the investigational nature of this study and must sign a study-specific informed consent form in accordance with institutional and federal guidelines prior to study entry.	• Pregnant or lactating women may not participate, owing to the embryotoxic effects of protocol treatment. • Women/men of reproductive potential may not participate unless they have agreed to use an effective contraceptive method. • Prior hepatic arterial therapy or hepatic radiation therapy. Prior surgical resection or ablation of liver metastases is acceptable. Patients must be at least 1 month beyond prior chemotherapy, PRRT, ablation, or surgery and must have recovered from all therapy-associated toxicities. • Active infection (symptomatic bacterial and fungal infection, newly diagnosed and/or requiring treatment) • Choledochoenteric anastomosis, transpapillary biliary stent, or sphincterotomy of duodenal papilla • Absolute contraindication to intravenous iodinated contrast agent (history of significant previous contrast agent reaction not mitigated by appropriate premedication) • Allergy to doxorubicin • Contraindications to arteriography and selective visceral catheterization: ○ Severe allergy or intolerance to contrast media, narcotics, sedatives, or atropine * ○* Bleeding diathesis not correctable by usual forms of therapy * ○* Severe peripheral vascular disease precluding catheterization • Contraindications to hepatic artery embolization: * ○* Portal vein occlusion without hepatopedal collateral flow demonstrated by angiography or portal hypertension with hepatofugal flow * ○* Hepatic encephalopathy

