#### Follow-up evaluation

Follow-up laboratory assays will be performed 3–3.5 weeks after the first embolotherapy session. If the patient remains eligible for further therapy, additional segmental or lobar embolization will be administered every 4 weeks until the entire disease area is adequately addressed. A maximum of four treatments can be performed per treatment cycle.

After the final embolotherapy session of the treatment cycle, serial clinic visits, QOL and NET symptom scores, laboratory assays including tumor marker(s), and triple-phase CT or MRI will be performed at 4–6 weeks posttreatment and then every 3 months ± 4 weeks (Fig. 1). If the patient remains within the eligibility criteria, repeat embolotherapy cycles can be performed when clinically indicated for intrahepatic progression. The second embolotherapy cycle will resume as described above. Total follow-up duration for each enrollee is at least 24 months. After this point, patients without disease progression will continue to receive clinical and imaging follow-up per institutional standard of care for the remaining duration of the trial.

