### Statistical analysis

Our analysis will be aimed at identifying any embolotherapy arm that is significantly inferior (or superior) to the others based on comparison of the primary outcome. Our null hypothesis assumes that the arms are equivalent, without preconceived ranking. The test will use a studentized range approach developed for phase II screening trials using survival data [26, 27]. We will estimate the survival hazard rate in each treatment arm and compute the range of log-hazard rates (largest minus smallest). We will then compare the observed range to the distribution of the range under the null hypothesis. If the observed range exceeds the 95th percentile of its null distribution, any group whose hazard rate differs by more than this critical value from the group with the lowest PFS hazard will be declared significantly worse.

For secondary outcomes including symptom relief interval, time to reembolization, overall PFS, and PFS for subsets of the study sample, we will estimate the survival distribution using the Kaplan-Meier method. Comparisons among groups will be performed using log-rank tests, and survival regression models will be developed to estimate treatment effects, adjusted for baseline variables that may affect treatment outcomes.

For continuous outcomes (e.g., quality of life and symptom scores), summary statistics (mean, SD, 95% CI) will be assessed for each of the study arms, and comparisons among arms will be performed using one-way analysis of variance and *t* tests. Regression models will be used to estimate treatment effects adjusted for baseline variables that may affect treatment outcome. Binary variables (e.g., biomarkers) will be tabulated by treatment arm and compared using the chi-square test. Logistic regression models will be used to estimate adjusted effects.

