## Discussion

Despite several decades of experience with embolotherapy for NET liver metastases, there remains uncertainty regarding the optimal treatment modality and a paucity of level I evidence. Compared with other primary and metastatic liver malignancies, NET liver metastases have superior oncologic outcomes with a median survival of 18–65 months from initial embolotherapy [4–6, 9, 10, 12, 20, 21]. The relatively indolent disease course and multimodality treatment approach have unique implications for determining the optimal liver-directed embolotherapy. The chosen technique should ideally not only achieve superior survival and local disease control but also have tolerable toxicity when repeated and used in combination with other therapies. The existing evidence base does not provide a clear answer regarding which embolotherapy best satisfies these criteria, reflected in lack of guideline recommendations specifying a specific embolotherapy technique [14–18].

The Randomized Embolization Trial for NeuroEndocrine Tumor Metastases to the Liver (RETNET) will be the first multicenter prospective RCT aimed at elucidating these questions regarding optimal embolotherapy technique. The results of this study will help refine the role of embolotherapy for NET liver metastases by determining which, if any, embolotherapy technique confers superior HPFS and/or safety profile between BE, lipiodol TACE, and DEB-TACE.

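### Time to reembolization by Kaplan-Meier and log-rank: an arm in which more progressing patients get no repeat cycle shows a longer interval, even with equal tumor control

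*Protocol article*

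**What the plan says.** The interval between embolotherapy cycles, compared among techniques, is listed under Secondary endpoints. The Statistical analysis section fixes its method: "time to reembolization, overall PFS, and PFS for subsets of the study sample, we will estimate the survival distribution using the Kaplan-Meier method". It continues: "Comparisons among groups will be performed using log-rank tests, and survival regression models will be developed to estimate treatment effects".

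The condition for a repeat cycle is in Follow-up evaluation: "If the patient remains within the eligibility criteria, repeat embolotherapy cycles can be performed when clinically indicated for intrahepatic progression". The criteria in Table 1 include limits that treatment or progression can breach, for example "Serum bilirubin ≤2.0 mg/dl" and "Liver tumor burden ≤ 70% of the total liver volume by visual estimate".

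After hepatic progression there is another route out. Of radiation, chemotherapy, biologic therapy and ablation, Study population says: "Patients also cannot receive these treatments until after the primary endpoint of hepatic progression is reached". From that point a different therapy can take the place of a repeat cycle.

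The article does not say how death, lost eligibility or a switch of therapy is handled for this endpoint.

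**The concern.** Reembolization needs two things: hepatic progression, and a patient who can still be treated and is still treated by embolization. The hazard of the event is the progression hazard multiplied by the probability of the second condition. Kaplan-Meier and log-rank applied to that event mix tumor control with treatability. An arm that leaves more patients with poor liver function at progression has a lower reembolization hazard and a longer curve, which a reader could take for better control.

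A difference in liver damage between arms is an open question in this trial. The Background notes: "Two retrospective series have suggested higher risks for biliary complications after DEB-TACE". At stake is the direction of a between-arm comparison on a listed secondary endpoint.

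**Working it through.** **The plan's own figures.** No figure is stated for time to reembolization. The HPFS figures supply the time scale: medians of 11 and 20 months, so 20/11 = 1.82 (stated as about 1.8).

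The stated power can be reproduced with exponential times, uniform 24-month accrual and 24 months' minimum follow-up. The event probability is 1 − [exp(−24λ) − exp(−48λ)]/(24λ). With a bland-embolization median of 11 months and HR 1.78 this gives 0.886 and 0.712, hence 60 × (0.886 + 0.712) = 95.9 events per pair. Power at two-sided 10% is Φ(√95.9/2 × ln 1.78 − 1.645) = 88.1%, against 87% stated. The overall test gives 91.1%, against at least 92% stated. The exponential set-up thus matches the plan's to within 2 points.

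**Closed form for reembolization.** Let λ be the progression hazard and i the share ineligible (or switched) at progression, censored at that time. The share i is assumed throughout, because the article gives none.

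- Reembolization hazard = λ(1 − i), so with equal λ the apparent HR is (1 − i₁)/(1 − i₂).
- 30% against 10%: 0.7/0.9 = 0.78. 20% against 10%: 0.8/0.9 = 0.89.
- Kaplan-Meier medians, both arms with a true HPFS median of 20 months: 20/0.7 = 28.6 against 20/0.9 = 22.2 months.
- If the arm with 30% ineligible is also the one that progresses faster, a true HR of 1.82 appears as 1.82 × 0.7/0.9 = 1.4.
- Proportion re-embolized at 24 months, HPFS median 11 months (24λ = 1.512), i = 30%: 1 minus Kaplan-Meier is 1 − exp(−0.7 × 1.512) = 65%. The actual proportion is 0.7 × (1 − exp(−1.512)) = 55%.

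**Does the handling matter?** Two arms of 60 with identical progression were simulated (4,000 trials; medians from 400,000 patients per arm), with an assumed median survival of 33 months in both. Ineligible progressors were either censored at progression or kept at risk. The percentage is how often log-rank at two-sided 10% (nominally 5% in this direction) declares the arm with more ineligible patients to have the longer interval.

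| HPFS median, months | Ineligible | Censored: medians, % | Kept at risk: medians, % |
|---|---|---|---|
| 11 | 10% vs 30% | 12.2 vs 15.8, 26% | 13.0 vs 20.0, 51% |
| 11 | 10% vs 20% | 12.2 vs 13.7, 13% | 12.9 vs 15.6, 21% |
| 20 | 10% vs 30% | 22.2 vs 28.4, 22% | 23.3 vs 36.2, 34% |
| 20 | 10% vs 20% | 22.3 vs 24.9, 12% | 23.3 vs 28.2, 16% |

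The direction is the same under both handlings.

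**Deaths.** The Discussion gives "median survival of 18–65 months from initial embolotherapy". Under exponential survival, 1 − 2^(−24/65) = 23% to 1 − 2^(−24/18) = 60% are dead by 24 months. With survival medians of 65 against 18 months, independent of progression, and no ineligibility, the Kaplan-Meier medians are 11.0 and 11.0 months and log-rank keeps about 5% in each direction. Only the proportion is wrong. 1 minus Kaplan-Meier at 24 months is 78% in both arms. The actual incidence, with death hazard μ, is λ/(λ+μ) × (1 − exp(−24(λ+μ))). That is 0.855 × 0.829 = 71% for the 65-month arm and 0.621 × 0.913 = 57% for the 18-month arm.

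**Eligibility lost before progression and independent of it** (10% against 30% by 24 months, HPFS median 11 months). If censored at loss there is no shift (11.1 against 11.0 months). If kept at risk the medians are 11.3 against 12.3 months.

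**The case against.** The strongest reply is that the article names an estimator and a test, not an event or censoring rule, and that such rules commonly sit in a full protocol or SAP. It is true that censoring is nowhere stated. A reader might infer that log-rank cannot accommodate these patients at all. That goes too far, because a log-rank test on a composite event accommodates them. What stands is narrower. For reembolization as the event, which is what the text names, both usual ways of treating ineligible progressors push the comparison the same way, so the difficulty lies in the stated method and not only in an unwritten rule.

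Other limits also stand:

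- A reader might infer that an arm with more deaths gains an advantage in the log-rank. The calculation does not bear this out unless death is related to progression.
- A reader might infer that an ineligible patient can never be re-embolized. Table 1 allows platelets and INR to be corrected, and infection or laboratory values may recover.
- Nothing in the article supports a 20-point gap in ineligibility between arms, and the biliary signal for DEB-TACE does not establish one.
- The Hypothesis section attaches durability to HPFS, not to this endpoint, and toxicity is compared separately, so a more toxic arm would be visible elsewhere.

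**Conclusion.** The concern holds for a secondary endpoint. With equal tumor control, the arm with more patients who progress without a repeat cycle, through lost eligibility or a switch of therapy, shows the longer reembolization interval under the stated analysis. The direction follows from the protocol's own condition for a repeat cycle.

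The size cannot be taken from the documents. Hazard ratios of 0.78 (30% against 10%) and 0.89 (20% against 10%) illustrate assumed rates and are not forecasts. They rest on exponential progression and on ineligibility arising at progression. Deaths distort the estimated proportion re-embolized, but they distort the arm comparison only through dependence on progression. The documents do not support predicting which arm would be flattered. The HPFS analysis and the sample size are untouched.

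**What to change.** In Statistical analysis, take time to reembolization out of the Kaplan-Meier sentence and specify:

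1. The Aalen-Johansen cumulative incidence of reembolization by arm, shown beside that of its competing events: death without reembolization, and hepatic progression without reembolization because of lost eligibility or a switch of therapy. Since some ineligibility is reversible, date the latter from the recorded decision not to repeat. Cumulative incidence of reembolization alone does not cure the direction, because an arm with more untreatable patients also shows fewer reembolizations. The curves must be read together.
2. The log-rank test on reembolization labelled as a comparison of cause-specific hazards, not to be read alone as durability.
3. A supportive log-rank test on the composite of reembolization, hepatic progression without a repeat cycle for the reasons above, or death.

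The cost is analysis wording and one data field, the reason no repeat cycle was given, best collected while the trial runs. Because repeat cycles follow intrahepatic progression, the composite overlaps heavily with HPFS and says little specific to reembolization, so it should stay supportive.

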### Data management and monitoring

Data management will be handled by the Clinical Research Computing Unit at the University of Pennsylvania. Study data will be entered in an ORACLE database. Data entry will be performed by study coordinators and investigators at each of the sites.

Triphasic abdominal CT and MRI images will be uploaded to the Imaging Core at the American College of Radiology in Philadelphia and undergo central review by independent, blinded diagnostic radiologists unaffiliated with the participating institutions.

For patients who withdraw following embolotherapy, reasonable efforts will be made to track adverse effects, follow-up imaging results, and survival through the medical record at the treating institution by their treating physician.

Data quality checks have been built into the ORACLE data collection instruments. All database information will be encrypted, and de-identified data will be used for analysis. All investigators will permit study-related monitoring, audits, and inspections by the ethics committee, IRB, sponsor, government regulatory bodies, and university compliance and quality assurance groups of all study-related documents (e.g., source documents, regulatory documents, data collection instruments, study data). Remote audits of 5% of the data from each site will be perfumed at 50% accrual and at completion of accrual.

### Ethical considerations and dissemination

The study protocol and any amendments will be submitted to a properly constituted independent ethics committee or IRB, in agreement with local legal prescriptions, for formal approval of the study conduct. The formal consent of a subject, using the ethics committee/IRB-approved consent form, must be obtained before that subject undergoes any study procedure. The consent form must be signed by the subject or legally acceptable surrogate and by the investigator-designated research professional. Unanticipated problems posing risks to subjects or others as noted above will be reported to the sponsor institution IRB.

Each subject is assigned a unique patient identification (PID) number in the ORACLE database. All research data and images are de-identified at the source and associated with the PID number.

The principal investigator is responsible for publication of the results of this study in whole or in part. Neither the complete nor any part of the results of the study carried out under this protocol, nor any of the information provided by the sponsor for the purposes of performing the study, will be published or passed on to any third party without the consent of the study sponsor. Any investigator involved with this study is obligated to provide the sponsor with complete test results and all data derived from the study.

## Discussion

Despite several decades of experience with embolotherapy for NET liver metastases, there remains uncertainty regarding the optimal treatment modality and a paucity of level I evidence. Compared with other primary and metastatic liver malignancies, NET liver metastases have superior oncologic outcomes with a median survival of 18–65 months from initial embolotherapy [4–6, 9, 10, 12, 20, 21]. The relatively indolent disease course and multimodality treatment approach have unique implications for determining the optimal liver-directed embolotherapy. The chosen technique should ideally not only achieve superior survival and local disease control but also have tolerable toxicity when repeated and used in combination with other therapies. The existing evidence base does not provide a clear answer regarding which embolotherapy best satisfies these criteria, reflected in lack of guideline recommendations specifying a specific embolotherapy technique [14–18].

The Randomized Embolization Trial for NeuroEndocrine Tumor Metastases to the Liver (RETNET) will be the first multicenter prospective RCT aimed at elucidating these questions regarding optimal embolotherapy technique. The results of this study will help refine the role of embolotherapy for NET liver metastases by determining which, if any, embolotherapy technique confers superior HPFS and/or safety profile between BE, lipiodol TACE, and DEB-TACE.

### Trial status

Patient enrollment started in March 2017 and was ongoing at the time the manuscript was submitted. Completion of accrual is expected to take 24 months.

## Abbreviations

BE: Bland embolization
CONSORT: Consolidated Standards of Reporting Trials
CT: Computed tomography
cTACE: Classical transarterial chemoembolization
CTCAE: Common Terminology Criteria for Adverse Events
DEB-TACE: Drug-eluting bead transarterial chemoembolization
EORTC: European Organization for Research and Treatment of Cancer
GI: Gastrointestinal
HPFS: Hepatic progression-free survival
INR: International normalized ratio
IRB: Institutional review board
MRI: Magnetic resonance imaging
NET: Neuroendocrine tumor
PFS: Progression-free survival
PID: Patient identification
PRRT: Peptide receptor radionuclide therapy
QOL: Quality of life
RCT: Randomized controlled trial
RECIST: Response Evaluation Criteria in Solid Tumors
RETNET: Randomized Embolization Trial for NeuroEndocrine Tumor Metastases to the Liver
SAE: Serious adverse events
SPIRIT: Standard Protocol Items: Recommendations for Interventional Trials
TACE: Transarterial chemoembolization
WHO: World Health Organization
